### Randomisation

Allocation will take place after baseline measures have been collected, and will be conducted by the study statistician, blinded to any identifying information. The statistician will randomly allocate schools stratified by geographical area and FSM scores (see Table 1) to intervention or control arm, using computer-generated random numbers.

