### Blinding

It is not possible for study participants to be blind to intervention status, or for the research team leading the outcome data collections as they will also have organised intervention delivery with the schools and conducted the process evaluation. However casual staff assisting with data collection and inputting the questionnaire data, the statisticians analysing the primary and secondary outcome data and the health economists undertaking the economic analysis will be blind to intervention status.

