### Sample size calculation

The study is powered to detect a mean change of 3 points on the primary outcome - the WEMWBS score among teachers. This difference has been chosen as the minimum meaningful change discussed in a WEMWBS user guide [38]. A change of 3 points is also close to the difference in mean baseline scores between the highest and lowest ranked schools in the pilot study. Sample sizes were calculated using the clustersampsi command within Stata, which accounts for the clustered nature of the data by including intracluster correlation coefficients (ICCs) in the calculation. Based on the pilot data [34] we assumed a WEMWBS ICC of 0.01 (0.00, 0.05), a mean of 50 teachers followed up per school (with a coefficient of variation of sample size of 0.5), and a standard deviation for WEMWBS of 8.4. A sample size of 24 schools (12 intervention and 12 control) will achieve 83 % power at the 5 % significance level for an ICC of 0.05 (the highest of the confidence intervals in the pilot ICC); this would rise to 98 % for an ICC of 0.02.

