#### Primary analysis

Repeated measures (random effects) models will be used to examine pattern of change in the primary outcome (teacher WEMWBS as a continuous measure) over baseline, one year and two year follow ups adjusted for stratification variables and additional appropriate variables. The models will include every teacher who has at least one measure (at baseline or either of the two follow-up periods), and are robust to data which are missing at random (MAR). Thus no imputation is needed for this analysis [39, 40]. Results will be presented as mean differences in the primary outcome between the trial arms, with 95 % confidence intervals and *p*-value.

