#### Secondary analyses

Analysis will include, linear (continuous outcomes), multinomial (ordinal outcomes) and logistic (binary outcomes) regression models depending on the outcome measure. They will be used to compare the outcome at follow up by arm, initially unadjusted for variables (accounting for clustering), then adjusted for baseline outcome and for school-level FSM and geographical area, as stratifying variables [41]. Then finally adjusted for important covariates such as age, gender and any other covariates that are not balanced at baseline.

For individual level outcomes that are measured at 12 and 24 months (e.g., PHQ-8), repeated measures models will be used, including a random effect for each individual, and random effects to allow for clustering by school. All individuals with at least one observation of the outcome measure will be included in the model for that outcome measure, under a Missing at Random (MAR) assumption.

For individual level outcomes that are only measured at 24 months (e.g., student WEMWBS), a regression will be used, with robust errors to account for clustering.

For school level outcomes that are measured at both 12 and 24 months (e.g., teacher absence), repeated measures models will be used. For outcomes at school level which are only measured at 24 months (e.g., student attainment), a simple regression will be used.

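### The last secondary-outcome model picks covariates because the arms differ on them at baseline, which is chance and says nothing about prognosis

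*Protocol article*

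**What the plan says.** The Secondary analyses section of the protocol article compares each outcome between arms in three successive models.

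1. The first is "initially unadjusted for variables (accounting for clustering".
2. The second is "then adjusted for baseline outcome and for school-level FSM and geographical area, as stratifying variables".
3. The third: "Then finally adjusted for important covariates such as age, gender and any other covariates that are not balanced at baseline".

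The section gives no criterion for calling a covariate unbalanced and no closed list of candidates, and it does not say which of the three models supplies the reported result.

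Three other sections bear on the point:
- Randomisation: "Allocation will take place after baseline measures have been collected".
- Blinding: those kept blind to intervention status include "the statisticians analysing the primary and secondary outcome data".
- Primary analysis: the model is "adjusted for stratification variables and additional appropriate variables". That list is open, but it contains no rule based on imbalance.

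**The concern.** Baseline measures are taken before schools are allocated, so a difference between arms on any of them is produced by the allocation alone. Its size says nothing about whether the covariate is related to the outcome, and that relation is what makes adjustment worthwhile. A strong predictor that happens to balance is left out, and an irrelevant variable that happens to differ is put in.

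Two things are at stake. One is precision: with 24 schools, each school-level covariate added also uses a degree of freedom. The other is that the model is not determined by the protocol. Two competent analysts with different ideas of balance would fit different models. For the logistic and multinomial analyses the matter goes further, because adjusted and unadjusted odds ratios estimate different quantities, so the three models are not interchangeable.

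**Working it through.** **The plan's own figure.** The only computable design figure is the power in the Sample size calculation section, and it is not in dispute. Inputs from that section: 12 schools per arm, a mean of 50 teachers followed up per school, coefficient of variation 0.5, SD 8.4, a difference of 3 points, and the headline power "for an ICC of 0.05 (the highest of the confidence intervals in the pilot ICC".

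- Design effect = 1 + ((CV² + 1)m − 1) × ICC = 1 + (1.25 × 50 − 1) × 0.05 = 4.075.
- Effective n per arm = 600 / 4.075 = 147.2.
- Two-sided 5% test, t with 22 df: power 83.4%, against a stated 83%.
- At ICC 0.02 the design effect is 2.23 and power is 97.7%, against a stated 98%.

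The stated power reproduces, so the same design effect can be used below.

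**How often the rule fires.** The document gives neither a threshold nor a number of candidates, so both are assumptions.

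*Flagging at p<0.05*, with k independent candidates: 1 − 0.95^k.

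| k | chance that at least one is flagged |
|---|---|
| 3 | 14% |
| 5 | 23% |
| 10 | 40% |

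*Flagging by standardised difference*, for a teacher-level covariate: SE = √(2 × design effect / 600). At ICC 0.05, SE = √(2 × 4.075 / 600) = 0.117. At ICC 0.01 the design effect is 1.615 and SE = 0.073.

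| threshold | covariate ICC | one covariate | at least one of 8 independent |
|---|---|---|---|
| 0.1 SD | 0.05 | 39% | 1 − 0.609^8 = 98% |
| 0.25 SD | 0.05 | 3.2% | 23% |
| 0.25 SD | 0.01 | 0.07% | 0.5% |

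So the same clause fires almost never or almost always, depending on a definition that is not given.

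**Type I error.** Null simulation at school level: 24 schools in 12 stratum pairs, 4,000 runs per setting. The third model had two fixed covariates plus any of four candidates that differed at p<0.05. Assumed inputs: baseline-outcome coefficient 0.3 or 0.6; joint covariate strength 0, 0.4 or 0.6.

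| quantity | range over settings |
|---|---|
| type I error, each model alone | 4.0-5.7% |
| third (imbalance-selected) model alone | 4.0-5.3% |
| at least one of the three models significant | 8.4-9.8% |
| the three models disagree on significance | 6.2-8.6% |
| at least one candidate flagged | 17-20% |

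The Monte Carlo standard error at 5% is √(0.05 × 0.95 / 4000) = 0.34 percentage points. For reference, three independent tests would give 1 − 0.95³ = 14.3%. The excess over 5% comes from free choice among models, not from the imbalance rule.

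**Precision.** The loss depends on whether a strong predictor is left to the trigger. In the simulations below there are 24 schools, six covariates and a 0.5 SD trigger; the structure and effect sizes are assumed.

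| set-up | pre-specified adjustment: type I error / power | imbalance-triggered: type I error / power |
|---|---|---|
| the only predictor is left to the trigger | 5.2% / 93% | 3.6% / 78% |
| as above, predictor R² 0.3-0.6, effect 1.0-1.2 SD | 4.6-5.3% / 77-99% | 2.4-3.9% / 60-81% |
| strong predictor always in the model | power 87-88% | 4.9-5.0% / 81-82% |

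The last row is closer to this plan, which always adjusts its second model for baseline outcome, free school meals (FSM) and area. There the loss is about 5-7 percentage points of power.

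**The case against.** The best defence is that the clause does little harm. The trigger uses baseline data only, gathered one to two years before the outcomes, so it cannot be steered by results. The analysing statisticians are blind to intervention status. The covariates most likely to matter (baseline outcome, strata, age and gender) do not wait on imbalance. The words initially, then and finally describe a progression rather than a licence to choose. Naming the headline model is commonly left to an analysis plan, which is not shown.

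Most of this stands, and it rules out several stronger readings:

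- *The effect is chosen after unblinding.* The Blinding section says otherwise. Coded arms are enough to judge imbalance and to compare three results, but that is not choice after unblinding.
- *The rule inflates the false-positive rate.* The simulations show the reverse or no change.
- *The rule will almost always fire, and power falls from 93% to 78%.* Both figures need assumed thresholds, covariate counts and prognostic structure. The power figure also leaves the one predictor to the trigger, whereas the second model here already has fixed adjustment.
- *The primary outcome is exposed.* The Primary analysis section has an open list but no imbalance rule, and an analysis plan can close that list.

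The defence does not remove the clause itself. It is an affirmative instruction, not a detail left out. An analysis plan that follows it inherits the weakness, and one that drops it departs from the protocol.

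**Conclusion.** The concern holds for one clause: the third secondary-outcome model selects covariates by chance imbalance instead of prognosis. The consequence is some loss of precision, about 5-7 points of power under the assumed set-up closest to this plan, and a covariate set that the document does not determine. The loss is larger only if a strong predictor is left to the trigger.

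Type I error for that model alone is roughly nominal or conservative. The 8.4-9.8% per outcome applies only if any of the three models may be taken as the result, a freedom that the text neither grants nor excludes. The simulation inputs are assumptions, not document figures. Sample size and trial conduct are unaffected.

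**What to change.** In Secondary analyses, delete the clause that admits other covariates because they are unbalanced at baseline. Put in its place a short closed list chosen in advance for expected prognostic value. Age and gender are already named for individual-level outcomes; for school-level outcomes, list school-level variables only.

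State that the second model, adjusted for baseline outcome and stratification factors, is the reported secondary result, and that the unadjusted and further-adjusted models are sensitivity analyses.

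Where baseline is already one of the repeated outcomes (teacher WEMWBS, and PHQ-8 if modelled the same way), do not also enter it as a covariate. That would use it twice and drop participants without a baseline measure, contrary to the stated inclusion of everyone with at least one measurement.

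The additional variables of the primary model can be listed in the statistical analysis plan. The cost is wording only, settled before outcome data are examined.

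### One random effect per teacher imposes a single correlation across baseline, year 1 and year 2; if correlation falls over two years, standard errors for baseline-referenced year-2 contrasts are somewhat too small

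*Protocol article*

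**What the plan says.** All places are in the protocol article.

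- **Secondary analyses.** For individual-level outcomes measured at 12 and 24 months, with PHQ-8 as the example, "repeated measures models will be used, including a random effect for each individual, and random effects to allow for clustering by school". No random slope and no residual correlation structure is named. The same section also describes adjustment for the baseline value of the outcome.
- **Primary analysis.** "Repeated measures (random effects) models will be used to examine pattern of change in the primary outcome", namely teacher WEMWBS over baseline and both follow-ups. A teacher with any one of the three measures enters the model, so baseline is a response. The models are said to be ones that "are robust to data which are missing at random (MAR"), and imputation is judged unnecessary for that reason. Results are mean differences between arms; the text does not say whether these are level or change contrasts.
- **Statistical analysis, opening paragraph.** Clustering by school may be handled by a random effect or by robust standard errors; repeated measures are handled by random effects.
- **Tests for interactions.** The time-by-intervention interaction will be examined.

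**The concern.** A model with one random intercept per teacher and independent residuals has two teacher-level variance parameters. It therefore implies the same variance at each wave and the same correlation for every pair of waves. The pairs here are not alike: baseline with year 1 and year 1 with year 2 are one year apart, baseline with year 2 is two years apart. Scores closer in time often correlate more strongly. If so, the fitted common correlation is an average that is too high for the two-year pair and too low for the one-year pairs, and the model-based variance of each change contrast is wrong accordingly.

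What is at stake is the confidence interval for the two-year effect on teacher WEMWBS and PHQ-8, wherever that effect is estimated relative to baseline. The missing-data argument depends on the same assumption. The section Participant retention and loss to follow up expects teachers to leave between waves and gives this as the reason for the repeated-measures design. With incomplete data, information passes between waves through the assumed covariance, so the likelihood argument under missing at random needs that covariance to be adequate.

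**Working it through.** **1. The plan's own figure.** Inputs from Sample size calculation: "The study is powered to detect a mean change of 3 points on the primary outcome"; "a standard deviation for WEMWBS of 8.4"; "a mean of 50 teachers followed up per school (with a coefficient of variation of sample size of 0.5"). Stated result: "A sample size of 24 schools (12 intervention and 12 control) will achieve 83 % power" "at the 5 % significance level for an ICC of 0.05". A two-sided test is assumed.

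- Design effect = 1 + ((0.5² + 1) × 50 − 1) × 0.05 = 4.075.
- Effective number per arm = 12 × 50 / 4.075 = 147.2.
- SE = 8.4 × √(2/147.2) = 0.979, and 3/0.979 = 3.06.
- Noncentral t with 22 df: power 83.4%, which agrees. At ICC 0.02 the design effect is 2.23 and power 97.7%, against the stated 98%.

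This calculation uses no within-teacher correlation, so it neither supports nor contradicts the covariance model.

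**2. What the single intercept estimates.** Assume equal variances, complete data, one-year correlations r1 (both pairs) and two-year correlation r2. The article gives neither. The fitted common correlation is

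ρ = (2·r1 + r2)/3.

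The variance of a change is proportional to 2(1 − correlation), so the ratios of model SE to true SE are

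- baseline to year 2: √[(1 − ρ)/(1 − r2)]
- baseline to year 1: √[(1 − ρ)/(1 − r1)]

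and the true two-sided error of a nominal 5% test is 2[1 − Φ(1.96 × ratio)].

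| r1 | r2 | ρ | Year-2 ratio | Year-2 error | Year-1 ratio | Year-1 error |
|---|---|---|---|---|---|---|
| 0.70 | 0.70 | 0.700 | 1.000 | 5.0% | 1.000 | 5.0% |
| 0.60 | 0.50 | 0.567 | 0.931 | 6.8% | 1.041 | 4.1% |
| 0.70 | 0.60 | 0.667 | 0.913 | 7.4% | 1.054 | 3.9% |
| 0.60 | 0.45 | 0.550 | 0.905 | 7.6% | 1.061 | 3.8% |
| 0.70 | 0.55 | 0.650 | 0.882 | 8.4% | 1.080 | 3.4% |
| 0.75 | 0.60 | 0.700 | 0.866 | 9.0% | 1.095 | 3.2% |
| 0.60 | 0.70 | 0.633 | 1.106 | 3.0% | 0.957 | 6.1% |

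The first row has no decay and no error. The last row reverses the direction.

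**3. In WEMWBS points.** Take r1 = 0.70, r2 = 0.60, ICC 0.05 and 60 teachers per school (Study population), so 720 per arm. Within-school variance = 0.95 × 8.4² = 67.03. SE = √[2 × 2(1 − correlation) × 67.03/720]:

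- model, correlation 0.667: 0.352
- true, correlation 0.60: 0.386
- ratio 0.352/0.386, which is 0.913 before rounding, as in the table

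Fitting the full school-plus-teacher model gives the same values. Constraining baseline means to be equal gives 0.916 (7.3%). An assumed staff-turnover pattern gives 0.925 (7.0%).

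**4. School-by-time variance present and modelled.** Suppose it is 1% of total variance, with 50 teachers per school. As fractions of total variance, each school's mean change has variance 2 × 0.01 + 0.95 × 2(1 − correlation)/50.

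- r1 = 0.70, r2 = 0.60: model 0.02 + 0.0127 = 0.0327; true 0.02 + 0.0152 = 0.0352; ratio 0.963; error 5.9%.
- r1 = 0.75, r2 = 0.60: model 0.0314; true 0.0352; ratio 0.944; error 6.4%.

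**5. Unequal one-year correlations.** With baseline–year 1 at 0.60, year 1–year 2 at 0.70 and baseline–year 2 at 0.55, ρ = 0.617. Both baseline-referenced SEs are then too small: ratio 0.979 at year 1 and 0.923 at year 2.

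**6. Joint time-by-arm test.** Under the decaying rows of the table, the two-degree-of-freedom test runs at 5.1-5.4%, because the over- and understatement largely cancel.

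**The case against.** The case against is substantial.

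- **The covariance form is not fully fixed.** Saying that a model includes a random effect per individual does not exclude a slope or a residual structure, and the primary-analysis text gives no form. A journal article may leave this to the analysis plan. This stands as a caution. Still, a random effect per individual is the only within-teacher term stated, and the plain reading is a single intercept.
- **Baseline may be a covariate for secondary outcomes.** The Secondary analyses section mentions baseline adjustment. On that reading only years 1 and 2 are responses, there is one correlation, and nothing is forced equal. This stands for PHQ-8. It does not fit the primary model, which admits teachers with only a baseline measure.
- **The reported effect may be a level difference.** With complete data, equal variances and free arm-by-time terms, a difference between arms at one wave is unaffected. This stands.
- **Robust standard errors are permitted.** Clustered on school they would correct these SEs, within the limits of 24 schools. However, for repeated individual outcomes the Secondary analyses section chooses school random effects and reserves robust errors for outcomes measured only at 24 months.
- **Permutation p-values are named as one option for interaction tests.** Where used, they would not rely on the working covariance. They do not repair confidence intervals.

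A reader might infer that the two-year interval will be too narrow and the year-1 interval too wide. The article does not support that: it reports no within-teacher correlation, and equal, reversed or uneven correlations remove or change the pattern. Nor has any bias under data missing at random been calculated; that point is one of principle.

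**Conclusion.** The point holds in conditional form. On the plain reading, with baseline as a response, the stated model imposes equal variances and a common correlation over unequal intervals. If the two-year correlation is below equal one-year correlations, baseline-referenced year-2 contrasts have model-based SEs about 7-13% too small over the assumed range, so a nominal 5% test runs at about 7-9%. A modelled school-by-time variance of 1% reduces this to about 6%. Size and direction rest on correlations that are assumed, not documented. The joint time-by-arm test is hardly affected, so the concern is with single change contrasts. The statement about data missing at random should be understood as conditional on an adequate within-teacher covariance. The change is worth making because the alternative is correct under decay, no decay or reversal, at very little cost.

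**What to change.** For continuous teacher outcomes (WEMWBS and PHQ-8 score) modelled with baseline as a response, replace the single teacher random effect with an unstructured within-teacher covariance over the three waves, and keep the school-level terms. State for each outcome whether baseline is a response or a covariate; where it is only a covariate, this change is not needed.

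The cost is three variances and three correlations instead of two parameters, so four more nuisance parameters and a slightly more complex fit. With 24 × 50 = 1,200 teachers expected at follow-up, this is a small burden, and little is lost if the correlations prove equal.

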#### Missing data

In the pilot study, missing data for teacher WEMWBS score was 1.6 % at baseline and 3.5 % at follow up, and for teacher PHQ-9 score was 7.4 % at baseline and 5.4 % at follow up. Missing data for student WEMWBS was 14.8 % at baseline and 10.9 % at follow up, and for student SDQ was 16.2 % at baseline and 12.7 % at follow up.

We will assess the impact of missing data and non-response on teacher WEMWBS and PHQ-8 outcomes and student WEMWBS and SDQ outcomes using an appropriate imputation model. If multiple imputation is used [42], imputation models will include all outcomes (baseline and follow-up), intervention arm, stratifying variables and a random effect for schools to allow for clustering, as well as any appropriate baseline covariates and interactions (see below). All secondary analyses will be repeated on the imputed datasets, and results combined using Rubin’s rules. We will also use sensitivity analyses to examine the impact of potential missing not at random (MNAR), by assuming that those with missing outcome scores had better/worse outcomes than equivalent individuals with complete data [43]. We will examine the sensitivity of our conclusions to missing outcome scores that are 20, 50 and 100 % SD worse than expected had they not been followed up, and similarly 20, 50 and 100 % SD better. We will also estimate the largest amount that would need to be added to/subtracted from imputed outcomes without changing the clinical interpretation of the trial.

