### Participant retention and loss to follow up

In the pilot study missing outcome data was largely due to participants not being present during data collection sessions. In this study we have built in time after the initial data collection sessions to follow up missing participants. Where possible second data collection sessions will be planned with students. It will be harder to ask schools to set aside more than one staff meeting for data collection, so teachers absent from the data collection session will be followed up by email and given the option of completing either an online survey or posting a paper one back to the study team. A certain number of participants will be lost to follow up due to leaving the school between baseline and follow up. For this reason our primary analysis will use a repeated measures design that includes all participants with any data (see below).

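### The missing-not-at-random shifts and tipping point name no arm; read as a common shift, they say little about the treatment effect when loss is similar in both arms

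*Protocol article*

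**What the plan says.** The primary analysis is a repeated measures model that the protocol article (Primary analysis) describes as robust under MAR and as needing no imputation. The Missing data section then sets out the one described analysis that departs from MAR. It proceeds "by assuming that those with missing outcome scores had better/worse outcomes than equivalent individuals with complete data". The sizes are "missing outcome scores that are 20, 50 and 100 % SD worse than expected had they not been followed up"; the same three sizes are then used in the favourable direction. A tipping point follows: "We will also estimate the largest amount that would need to be added to/subtracted from imputed outcomes". The stated limit is that the clinical conclusion stays the same.

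Neither the shifts nor the tipping amount is tied to an arm, and no scenario sets one arm against the other. If multiple imputation is used, "imputation models will include all outcomes (baseline and follow-up), intervention arm, stratifying variables", so imputed values before shifting already reflect the arm.

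On the amount of loss, the section reports that in the pilot "missing data for teacher WEMWBS score was 1.6 % at baseline and 3.5 % at follow up", not split by arm. Participant retention and loss to follow up adds: "A certain number of participants will be lost to follow up due to leaving the school between baseline and follow up".

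**The concern.** A treatment effect on a mean is a difference between arms. Adding the same amount to missing scores in both arms largely cancels in that difference, so the analysis can leave the result untouched however large the shift. What could bias the comparison is that missing teachers in one arm differ from their MAR predictions in a way that those in the other arm do not.

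That is plausible here. The Abstract and Background link inadequate support and poor mental health to health-related exit or retirement, and school-level retirements and resignations are recorded as outcomes, so the intervention may affect who leaves. Under Blinding, participants and the team leading data collection know the allocation, so willingness to respond may also differ by arm. Overall loss could match while the kind of teacher lost does not.

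At stake is whether the trial's stated check on MAR would tell readers anything about the primary result.

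**Working it through.** **The plan's own figures.** The protocol states no result for this sensitivity analysis, so there is none to reproduce. The SD and target difference come from the Sample size calculation, whose power figures do reproduce. With design effect 1 + ((0.5² + 1) × 50 − 1) × ICC and a t-based calculation on 22 df, power is 83.4 % at ICC 0.05 (stated 83 %) and 97.7 % at ICC 0.02 (stated 98 %).

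**Inputs**
- SD 8.4 and target difference 3 points (Sample size calculation).
- Shifts of 0.2, 0.5 and 1.0 SD, that is 1.68, 4.2 and 8.4 points (Missing data).
- Missing fraction, low: 3.5 % (pilot teacher WEMWBS at follow-up).
- Missing fraction, higher: (60 − 50)/60 = 16.7 %, from about 60 teachers per school (Study population) and a mean of 50 followed up (Sample size calculation). This is an inference; the protocol does not state it as a loss rate.
- Unequal loss of 25 % v 20 %, 30 % v 20 % and 40 % v 20 %: assumptions for illustration.

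**Formula.** Let p be the missing fraction and δ the shift, with I for intervention and C for control. For a difference in means:

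change in effect = p_I × δ_I − p_C × δ_C

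For a common shift δ this becomes δ × (p_I − p_C), which is zero at every δ when p_I = p_C.

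**Reduction in the effect for a 1 SD (8.4-point) shift, in WEMWBS points**

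| Missing, I v C | Common shift, worse | Intervention only, worse | Opposite (I worse, C better) |
|---|---|---|---|
| 3.5 % v 3.5 % (pilot) | 0 | 0.29 | 0.59 |
| 16.7 % v 16.7 % (inferred) | 0 | 1.40 | 2.80 |
| 25 % v 20 % (assumed) | 0.42 | 2.10 | 3.78 |
| 30 % v 20 % (assumed) | 0.84 | 2.52 | 4.20 |
| 40 % v 20 % (assumed) | 1.68 | 3.36 | 5.04 |

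For example, 8.4 × 0.035 = 0.29; 8.4 × 10/60 = 1.40; 8.4 × (0.30 − 0.20) = 0.84. At 16.7 %, the smaller shifts of 0.2 and 0.5 SD give 0.28 and 0.70 in one arm, and 0.56 and 1.40 in opposite directions.

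**Simulation check.** 2,000 simulated trials per scenario, 12 schools per arm, ICC 0.05, true effect 3, school means compared by t-test, shifted scores treated as observed:
- 20 % missing per arm, no shift: mean effect 3.04, SE 0.93, 86 % significant.
- 20 % per arm, common 1 SD shift: 3.04, SE 0.96, 86 % significant.
- 30 % v 20 %, common 1 SD shift: 2.17, 57 % significant.
- 20 % per arm, 1 SD shift in the intervention arm only: 1.29, 25 % significant.

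**Tipping point.** The amount that removes the 3-point effect is:
- Common shift, equal loss: no finite value.
- Common shift, 5-point gap in loss: 3/0.05 = 60 points, beyond the whole WEMWBS range of 70 − 14 = 56.
- Difference between arm shifts, 16.7 % missing in each: 3/(10/60) = 18 points, or 18/8.4 = 2.1 SD. This is finite and can be judged for plausibility.
- Difference between arm shifts, 3.5 % missing in each: 3/0.035 = 86 points, out of reach, which would then be real reassurance.

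**The case against.** The strongest reply is that the article never says the shift is the same in both arms. A reader might infer that the plan imposes one common shift and so will always look reassuring. The documents do not support that. The text leaves the arm open, the shifts and tipping point could be run by arm, and a statistical analysis plan that is not shown may say so. The tipping-point sentence even presupposes that some amount would change the interpretation, which fits poorly with a common shift under equal loss. Nor does any section assume equal loss. If the intervention changes how many teachers leave, loss may differ, and a common shift then has effect: 0.84 points at 30 % v 20 %, and 1.68 at 40 % v 20 %.

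The size can also be challenged. The only stated missing rate for teacher WEMWBS at follow-up is the pilot's 3.5 %, at which even opposite 1 SD shifts move the effect by only 0.59. The 2.8 figure needs both the inferred 17 % and missing teachers whose departures from MAR lie 2 SD apart between arms.

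These points stand and limit the claim, but do not remove it. The article does not leave the matter wholly to a later document: it fixes the sizes, the directions and the tipping-point target. A common shift remains the natural reading of a rule that addresses everyone with missing scores and seeks a single amount. The dimension that most directly tests the treatment comparison is not among those fixed.

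**Conclusion.** The concern holds conditionally. Run as most naturally read, and with similar loss in the two arms, the analysis says little about arm-dependent departures from MAR, and its tipping point is very large or has no finite value. With clearly unequal loss it is informative.

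The effect that arm-specific shifts could reveal at 1 SD ranges from 0.29 points (one arm) and 0.59 (opposite) at 3.5 % missing to 1.4 and 2.8 at about 17 %. It matters in proportion to the loss that actually occurs. Exact cancellation applies to a simple difference in means on a continuous scale. Covariate-adjusted models, and models for binary or ordinal outcomes, may move slightly under a common shift. This is a worthwhile improvement to a sensitivity analysis, not a flaw in the primary analysis itself.

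**What to change.** In the Missing data section, state that the existing 20, 50 and 100 % SD shifts will also be applied separately by arm: intervention only, control only, and in opposite directions. Keep the common shift as one scenario, since it is informative when loss differs. Define the tipping point on the difference between the two arm shifts. Say explicitly that this covers the primary teacher WEMWBS contrast; teacher WEMWBS is already among the outcomes listed for missing-data assessment. Report missing fractions by arm beside the results so that readers can see which scenarios have leverage.

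The cost is a few more runs of the same imputation code and a somewhat longer sensitivity table. No extra data are needed.
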